**Preparation for venipuncture blood collection**

- Examination gloves should be worn by the licensed phlebotomist any time the potential for contact with blood exists.  Multiple pairs of nitrile gloves will be provided in the packing kit.
- Open the ziplock back containing the blood collection materials.
- Unfold the sanitary bench paper and place it on an even surface and lay contents of the blood collection kit out.
- Extend the patient’s arm and inspect the antecubital fossa and forearm. Locate a vein of good size that is visible and straight. Vein should be visible without applying the tourniquet.
- Apply tourniquet approximately 4 or 5 finger widths above the venipuncture site.
- Swab the skin where venipuncture will occur with isopropyl alcohol wipes. Allow the alcohol to dry.
- Insert the needle into the vein and collect blood into each tube (K2 EDTA, serum separator tube, plasma separator tube, PAXgene DNA tube, PAXgene RNA tube). A maximum of 2 venipunctures can be attempted per quarterly phlebotomy visit.

**Filling the Collection Tubes**

- Upon filling each tube, invert the tube 8-10 times to activate clotting in the serum separator tube, mix anticoagulant with the blood specimen for K2 EDTA or plasma separator tube, or improve efficiency of cell lysis and DNase/RNase deactivation in the PAXgene tubes..
- An adhesive bandage should then be applied to the punctured vein/skin.

**Shipping Blood Sample to ALS TDI**

- Plasma separator tubes and serum separator tubes will be centrifuged by on-site phlebotomists.
- Following any necessary centrifugation steps, each stoppered blood collection tube should be inserted into a Therapak foam tube holder. All foam encased blood sample tubes should then be placed into the biohazards zip lock bag prior to placing the bag into the NanoCool Cold Shipping Box.
- The NanoCool Cold Shipping Box should then be activated to induce cooling by pressing a button on the center of the underside of the lid of the Styrofoam inner box. The lids should then be placed firmly into the Styrofoam inner box.
- The NanoCool Cold Shipping Box containing blood should be dropped off to the nearest Fedex location by the phlebotomist for return.

Blood Sample Collection

Blood collection will be limited to 18 months from the time of a consented baseline blood draw. The investigator and study staff have discretion to determine that an individual should no longer be requested to give blood samples earlier than 18 months if they have concerns that an individual can no longer give continued consent.

**A3.3.8 Collection of Voice Recordings for Phase I and Phase II Participants**

Voice recordings will be collected in the same fashion in both phase I and phase II of the study.

Voice data will be collected at least once a month using an automated system to compare the sensitivity of unbiased voice recording assessments to web based ALS FRS self-reporting questionnaire.

The Speech Tracking part of the Precision Medicine Program is meant to help add greater sensitivity to interpreting changes in speech by asking participants who are able to record phrases monthly. Use of serial voice recordings was chosen based on research suggesting its ability overtime as a tool to determine changes in a person's ability to speak verbally.

Participants will be required to log into their portal, using their privately protected user name & password. They then provide the telephone number where they can be reached. An automated system will call them within one minute. They would be asked to say any five of the phrases described in Appendix A.

Examples:

- - Who are you talking about?
  - I have no idea.
  - Is she coming?
  - It was nice of you to come today.
  - I don’t remember it being all that hard.

Then hit the # button. The automated system will then thank them and confirm the recording has been made or send them an email if it was not successful.

Alternatively, people could record themselves and send it to me at PMP program Email address [contact] using a MP3 or an Audio recording. I can upload it to their private folder.

Recording:

- Speak in your normal manner
- Start recording
- Pause for 10 seconds at the beginning of the recording.
- Read each phrase aloud as it is presented.
- Pause for 10 seconds at the end of the recording.
- Stop and save your recording
- Send your recording to this email monthly.

Participating in the Voice Recording of the study is completely optional.

Attached please find the screenshots that would guide them through the process.

[figure not shown]

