#### A3. DESCRIPTION OF RESEARCH PROTOCOL

**A3.1: Overview**

ALS TDI is conducting this study to identify new potential drug targets for ALS and develop new end points for ALS clinical trials. The objectives of this proposal are unique in that it will link clinical phenotype (disease onset and progression over time) with detailed genomic analysis (genome sequence of the participant) and the generation of pluripotent stem cell lines for drug development analysis in the research setting. Blood and skin samples will facilitate these objectives: Blood for DNA sequencing, and molecular analysis, and skin biopsy for generation of pluripotent stem cell lines. The program will assess disease progression by the online collection of data from a self reported ALS Functional rating scale (ALS FRS) questionnaire. The ALS FRS monitors the ability to perform common daily tasks and is used in most ALS clinical trials. Remote voice recording will be collected over the phone to monitor changes in voice patterns over time. Wearable technologies will be used to assess daily activity and exercise compared to ALS FRS.

The proposal will be divided into two phases of participant recruitment.

In phase I of the proposal 300 participants will be recruited over 12 to 18 months to participate in all aspects of the proposal including genomic sequencing, development of iPS cell lines, collection of medical and demographic data, self reported ALS FRS, voice recordings and collection of data from wearable technologies.

In the second phase of the proposal (extension phase) an additional 700 early stage ambulatory participants will be recruited for the collection of medical and demographic data, self reported ALS FRS, voice recordings, and collection of data from wearable technologies. The goal of the extension phase is to increase the power to detect disease progression and compare the gold standard outcome measure to predict disease progression in ALS (ALS FRS) to novel outcome measures (voice recordings, and wearable technologies). Blood samples maybe requested from participants on a quarterly basis during the study for genome sequencing and biomarker studies.

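### Serial voice recordings are not held to one phrase set or one recording channel within a participant, so voice slopes will be noisier and may be biased

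*Protocol*

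**What the plan says.** Section A3.3.8 describes two ways to make a voice recording.

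- **Telephone.** The participant logs in to the portal and gives a number, and "An automated system will call them within one minute". On content: "They would be asked to say any five of the phrases described in Appendix A". The five phrases printed below that sentence are labelled as examples, so they are not a required set.
- **Self-recording.** "Alternatively, people could record themselves and send it to me at PMP program Email address". MP3 or any other audio format is accepted, and the file is to be sent monthly. The instruction on content is "Read each phrase aloud as it is presented". It does not say which phrases are presented or whether they repeat.

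The purpose is stated in two places. Section A3.1 says "Remote voice recording will be collected over the phone to monitor changes in voice patterns over time". Section A3.3.8 says "Voice data will be collected at least once a month using an automated system", with the aim "to compare the sensitivity of unbiased voice recording assessments to web based ALS FRS self-reporting questionnaire".

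The visible text has no rule that a participant repeats the same phrases, keeps to one route, or has the phrase set and route recorded. Section A3.3.9, on the accelerometers, does require participants to keep to a set timing and order of movements, and gives data integrity as the reason.

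**The concern.** The voice measure is a serial comparison of each person with himself or herself. Anything that alters the recording other than speech function enters the slope. Two such things are left open: what is said, and the equipment through which it is captured. A telephone line and a self-made file can differ in bandwidth, compression and microphone, and different phrases can differ in length and difficulty.

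Voice is one of the two new outcome measures that the extension phase sets against ALS FRS (section A3.1). If its slope carries avoidable noise or an artificial shift, voice could look less sensitive than ALS FRS, or sensitive in a different way, because of how the recordings were made. An analysis plan can repair this only in part, since it cannot standardise recordings already taken.

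**Working it through.** The protocol gives no sample size, SD or effect size for voice, so there is no figure to reproduce. The check has two parts: setting the text side by side, and an illustration under stated assumptions.

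**1. The text side by side**

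| Feature | Voice (A3.3.8) | Purpose or parallel rule |
|---|---|---|
| Content | any five phrases from a list | accelerometer task: order and timing fixed (A3.3.9) |
| Channel | automated call, or emailed file | over the phone (A3.1); automated system (A3.3.8) |
| Use | recordings at least monthly | change over time (A3.1); unbiased comparison with ALS FRS (A3.3.8) |

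The emailed file fits neither the telephone description in A3.1 nor the automated-system description in A3.3.8. Free choice of content sits badly with calling the assessment unbiased.

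**2. Random variation of phrase or channel**

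Assume monthly recordings and a least-squares slope for each participant. Let the error SD be σ and let phrase or channel add an independent SD of r·σ, unrelated to time. The slope is then unbiased, and the error part of its variance is

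σ²(1 + r²) / Sxx,

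so the corresponding standard error is multiplied by √(1 + r²).

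- r = 0.5: √1.25 = 1.12
- r = 1: √2 = 1.41

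These factors apply to the measurement-error part of a participant's slope. True differences in slope between participants are not inflated.

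**3. A shift related to time or disease**

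Take months 0 to 18; the 18 months of participation come from section A3.3.2. The mean time is 9 and Sxx = Σ(t − 9)² = 2 × (1² + … + 9²) = 2 × 285 = 570. Scale the true total change over 18 months to 1, so the true slope is 1/18. Let phrase set or channel change once, at month k, moving all later values by a share s of the true total change. The relative error in the fitted slope is

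s × [Σ over t ≥ k of (t − 9)] / 570 × 18.

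- k = 9: the sum is 0 + 1 + … + 9 = 45, and the multiplier is 45/570 × 18 = 1.42.
- k = 3: the sum is 24, and the multiplier is 24/570 × 18 = 0.76.
- k = 15: the sum is 6 + 7 + 8 + 9 = 30, and the multiplier is 30/570 × 18 = 0.95.

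| Shift s (assumed) | Switch at month 3 | Month 9 | Month 15 |
|---|---|---|---|
| 5% | 3.8% | 7.1% | 4.7% |
| 10% | 7.6% | 14.2% | 9.5% |
| 20% | 15.2% | 28.4% | 18.9% |

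A mid-study shift of 0.20/1.42, or about 14% of the total change, gives a slope error of 20%. That is the smallest slope change section A4 calls meaningful, though A4 says so for ALS FRS; here it is only a yardstick.

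The sign depends on the shift. A shift against the decline flattens the slope, and a shift with it steepens the slope. The result is for one participant. If a share f of participants shift alike and all have the same true total change, the mean slope moves by f times the figure in the table.

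**The case against.** The strongest reply is that the text does not show the harm actually occurring.

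- **Month-to-month switching is inferred.** Nothing invites participants to change route or phrases each month. The possibility follows from an open alternative with no restriction. This limits how often the problem can be assumed to occur, but does not remove it.
- **Free choice is stated only for the telephone route.** The self-recording instruction implies that phrases are presented to the speaker. Appendix A and the screenshots are not shown and could narrow the choice. The governing sentence still leaves the five open.
- **Part of it is recoverable.** The audio reveals which phrases were spoken, and emailed files arrive separately and are uploaded by hand. Adjustment afterwards is therefore possible, but it does not restore a constant stimulus.
- **Voice is optional and carries no power claim.** This lowers the weight of the point. The comparison with ALS FRS remains a declared aim.
- **Fixed phrases invite rehearsal.** This is a fair cost, but a serial comparison needs a constant stimulus.

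Three stronger readings are tempting and are not supported. First, a reader might take "Voice recordings will be collected in the same fashion in both phase I and phase II of the study" as contradicted by the two routes. That sentence says only that the two phases share one procedure, and both phases have the same two options. Second, a reader might infer from the examples, which run from 3 to 8 words, that recordings could differ almost threefold in length. The five distinct printed phrases give a single total of about 7 + 6 + 4 + 9 + 11 = 37 syllables, and a wide range would need an Appendix A that is not visible. Third, a reader might conclude that the voice slope is biased towards no change. That requires drift to easier phrases as speech worsens, which is plausible but which no passage shows.

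**Conclusion.** The point holds as a weakness in how the voice task is specified. The protocol asks for an unbiased serial measure but does not hold phrases or channel constant within a participant and has no visible rule to log them, although it fixes the accelerometer task for the sake of data integrity.

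The size depends on behaviour that the protocol does not describe. Random variation costs precision only, as in step 2. Variation linked to time or disease biases the slope by an amount that depends on the assumed shift and its timing, as in step 3, and in a direction that cannot be stated in advance. With phrase and channel unrecorded, the two cases would be hard to tell apart. The change is worth making before recordings accumulate, but the text does not establish that the voice comparison is invalid.

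**What to change.** In section A3.3.8:

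1. Replace the rule allowing any five phrases with one fixed set of five, in fixed order, at every recording and for both routes.
2. Make the automated call the default. Keep a participant who self-records on that channel.
3. Log the phrase set and the channel for every recording.
4. If a participant does switch channel, adjust for the switch in the slope analysis and do not exclude those recordings by default, because switching may itself be related to disease.
5. Bring the descriptions of the route in sections A3.1 and A3.3.8 into line with each other.

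The cost is a change to the call script and the self-recording instructions, plus a portal field for phrase set and channel. The downside is fewer distinct phrases per participant and some possible rehearsal effect over 18 months.

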**A3.3.9: Collection of Data from Wearable Technologies (Accelerometers) from Phase I and Phase II Participants**

Collection of data from wearable technologies will be the same for both phase I and phase II of the study.

Accelerometer data will be collected for one week per month to compare the sensitivity of unbiased movement to data to web based ALS FRS self-reporting questionnaire.

ALS is a complex disorder, where the site of onset and progression rate of the disease can vary greatly from person to person. The primary way that the disease is tracked in the clinic is using the ALSFRS-R score, which asks a series of questions about an individual's ability to conduct tasks, such as walking, grooming or feeding oneself. These questions help to asses a person's ability to move their hands, arms, feet and legs; areas often affected first in lumbar onset ALS. However, we believe that we can add greater sensitivity to these measures by asking that Patients to conduct a series of exercises using accelerometers on or around the same time they complete the ALSFRS-R score. Videos of these exercises are available online to help individuals complete the movement protocol.

The movement component of the study invites participants to wear accelerometers on their wrists and on their ankles for 1 week per month. During that week participants would perform a series of movements on three days of the week, whilst seated. They would then send the accelerometers back to ALS TDI in the FED EX Envelope provided. One month later the accelerometers will arrive at their doorstep. They would again wear them for a week and perform the movements for 3 days taking a day of rest between each day of exercise.

Attached is a hyperlink to a video we have created to assist participants in performing the movements. <https://www.youtube.com/watch?v=4G5JaRHxFYM>

We invite participants to participate in this for 18 months or as long the participant desires. If participants desire to withdraw from any elements of the study protocol at any time, they may.

*Step by Step Instructions*

The movements are timed in 45 second increments, and are done in a particular order to isolate motion in each limb one at a time. For the integrity of the data our team will read from your trackers, it is essential that you follow the timing and order of the movements. So please follow “[name]” exactly as he does the movements. Please do all of the motions to the best of your ability. If you experience pain or discomfort while doing any of these motions, either slow down or stop all together and rest out the remainder of the 45 second period. If you cannot do a particular motion to the full extent, please do what you can comfortably. If you cannot do a motion at all, rest during that particular segment.

**After you have identified the Trackers by looking on the back of the device, RW (right wrist), LW (left wrist), RA (right ankle), LA (left ankle) please wear them on the assigned limbs.**

Please make sure the trackers are firmly on your wrists and ankles (but not too tight)

Sit in a comfortable chair with a straight back. It’s ok to sit in a wheelchair.

- To start the exercise set, sit perfectly still for 45 seconds with your arms either at your sides or resting on the arms of the chair. **Get ready to start with your RIGHT LEG exercise in 3, 2, 1**
- (Next), begin your first movement which is to extend your right leg as high as you can and then lower it. Repeat this movement as many times as you can for 45 seconds. Be sure to keep the rest of your body still while you kick your leg. **10 seconds to rest**
- (Then) sit absolutely still for 45 seconds. **Get ready to start with your LEFT LEG exercise in 3, 2, 1**
- (Next) extend your left leg as high as you can, then lower it. Repeat this motion as many times as you can for 45 seconds. Be sure to keep the rest of your body still. **10 seconds to rest**
- Then sit absolutely still for 45 seconds **Get ready to start with your RIGHT ARM exercise in 3, 2, 1**
- (For the third motion), remain seated and swing your right arm out and over your head as high as you can; then lower it. Repeat this movement as many times as you can for 45 seconds. As before, keep the rest of your body still. **10 seconds to rest**
- Then sit absolutely still for 45 seconds. **Get ready to start with your LEFT ARM exercise in 3, 2, 1**
- (For the fourth motion,) remain seated and swing your left arm out and over your head as high as you can; then lower it. Repeat this movement as many times as you can for 45 seconds. **10 seconds to rest**
- Then sit absolutely still for 45 seconds. **Get ready to start with your BEND OVER exercise in 3, 2, 1**
- (For the fifth and final movement), from the seated position, bend over at the waist as if you are going to touch your toes with your hands and then sit back up against the chair. Repeat this movement as many times as you can for 45 seconds. **10 seconds to rest**
- Finally, sit absolutely still for 45 seconds, and then your exercise session is complete.

#### A4. STATISTICAL CONSIDERATIONS

Sample Size Justification: This is a research proposal with no prior knowledge of samples size estimates to determine the number of samples required to correlate genetic background to phenotypic outcome. Given that 90% of ALS cases are sporadic in nature with no known genetic mutation we are assuming it will take greater than 100 established cell lines and genomic sequences to allow un supervised clustering of phenotypic outcomes to genomic sequence. The goal of this phase is to build the tools and data integration systems necessary to perform a first pass analysis of genomics data to clinical phenotype and phenotypic analysis of a patients iPS lines when challenged with exogenous stimuli.

**Rationale around enrolling 700 participants in the second phase and collecting 10,000 data points:**

The most common primary end point in ALS clinical trials is ALS FRS. According to post hoc analysis on dozens of ALS clinical trials it takes 450 patients enrolled in a 12 month study to detect a 30% change in the slope of monthly reported ALS FRS. In order to detect meaningful changes in ALS disease progression slope as small as 20%, a cohort as large as 700 people with ALS would be required. The ALS FRS is a 12 point questionnaire with each question scored from 0-4, 4 being a perfect score. This is then summarized into a single score with a maximal value of 48 points per month for a perfect score. This represents 100,000 data points summarized to 8,400 individual scores over 12 months for 700 patients. In order to compare monthly reported ALS FRS with a potentially new outcome measure such as data from accelerometers the study will require a similar design to compare ALS FRS to accelerometers. The goal of the extension study is to enroll a second cohort of participants, a validation cohort, to collect 15,500 data points for ALS FRS and accelerometers in order to determine the sensitivity of these two potential outcome measures in a statistically meaningful way.

[figure not shown]

Data Analysis: ALS TDI has a robust data management system that assigns a unique identified and barcode to each tissue sample that is generated from any source. Each unique identifier can then have multiple clinical attributes associated with it including age, gender, age of diagnosis, site of onset, medication history, tissue type etc. ALS TDI has robust genomics capabilities including Affymetrix RNA profiling and whole genome sequencing data infrastructures built in SciTegic Pipeline pilot and a backend using Bioconductor and R code. Data from the project will be entered into these systems for downstream data quality control and processing. The Bioconductor packages have a suite of clustering tools to analyze multidimensional complex data structure to identify patterns in genomics, RNA profiling and clinical data obtained from this project.

The scientific rationale around control group will not be a 1:1 basis but would be of scientifically meaningful controls for example a twin of a participant with spontaneous ALS.

Data Follow Up:

There will be no specified end-time that individuals would be expected to stop reporting data online and the length of their participation in this portion of the research is at their discretion. However if a person would like to withdraw or cease to participate they may do so by calling [name] [name], or by emailing either: [[contact]](mailto:[contact])

Or [[contact]](mailto:[contact])

Participation is voluntary and there is no penalty and no loss of benefits for refusing to participate or withdrawing.

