# A2. PURPOSE OF PROTOCOL

**Goals of the Proposal**

There are two aims associated with this proposal. The first aim is to characterize the relationships between clinical phenotype through a series of questionnaires, genetic background, representation of phenotype in induced pluripotent stem cells and correlation to drug response in ALS patients. The second aim of this proposal is to identify new end points for ALS clinical trials by comparing the self reported ALS Functional Rating Scale (ALS FRS) to patient voice recordings and data collected from wearable technologies (accelerometers).

In the first phase of the study these goals will be accomplished by obtaining a patient’s consent to collect tissue samples (blood) for DNA sequencing and molecular profiling (RNA and protein) and a skin biopsy to develop an induced pluripotent stem cell line (iPS) for banking and high content drug screening at ALS TDI.

In this phase of the study participants will also be asked to report ALS FRS and provide a voice recording on a monthly basis and to wear accelerometers on their wrists and ankles for one week per month to collect unbiased movement data. These data will be compared to the ALS FRS questionnaire, a self-reporting web based questionnaire to monitor disease progression.

A database will be developed to link a patient’s genetic data, molecular data, and high content screening data with disease progression assessment methodologies.

In the second phase of the study (Extension Program) an additional cohort of early stage ambulatory participants will be recruited to increase the power to detect changes in disease progression using the data from a series of questionnaires, self reported ALS FRS, voice recordings, and wearable technologies (accelerometers).

300 participants will be recruited in the first phase of the study and 700 participants will be recruited in the second phase of the study in order to obtain statistically meaningful data for a total of 1000 participants.

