**Consent Phase II study participants**

There is no site visit or clinical visit associated with phase II participants.

If a participant responds to the recruitment announcement they will have provided their name, email address, and phone number.

The system will send a text message to the participant’s phone with a pin number and URL to log into a secure webportal with their preliminary information. The webportal will house all of their data for the study. The text message will serve as an authentication of the identity of the participant.

The webportal will be broken into sections. At the bottom of each section there will be a statement asking if the participant understand all in information provided in that section with a check box to check in order to move on. If a participant has questions an email link and phone number will be provided to contact a study coordinator to clarify information.

The following sections will be broken down:

- - Section I: Overview of the study, its rationale and objectives, and that participants will be asked to participate in the study for 18 months or until they are no longer able. They can stop at anytime.
  - Section II: Describe the rationale and purpose behind, the genome sequencing.
  - Section III: Describe the rationale and purpose for the development of induced pluripotent stem cell lines.
  - Section IV: Describe the rationale and purpose behind collecting monthly self reported ALS FRS.
  - Section VI: Describe the rationale and purpose on collecting monthly voice recordings.
  - Section VII: Describe the rationale and purpose behind collecting monthly accelerometer data.
  - Section VIII: Describe the rationale and purpose behind asking participants to fill out the demographic and medical questionnaires.
  - Section IX: There are minimal risks associated with participation in the study.
  - Minor discomfort may be experienced during the in-home venous blood collection.
  - Section X: There are no treatments being administered as part of the study.
  - Section XI: Participation in the study is voluntary. A decision to not participate will not result in any penalty or loss of benefits.
- Once all the sections have been read and the boxes checked that the participant understands all the information for the study they will be asked to sign the online consent form
- When the forms arrive back into our system the consent form is then signed electronically by the PI, [name].

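### The protocol's 700 participants for a 20% change in ALS FRS slope do not follow from its own benchmark of 450 for 30%: with other assumptions unchanged, 20% needs about 1,013, and 700 corresponds to about 24%

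*Protocol*

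**What the plan says.** The paragraph in section A4 on the rationale for 700 participants cites post hoc analysis of ALS trials, according to which "it takes 450 patients enrolled in a 12 month study to detect a 30% change in the slope of monthly reported ALS FRS". The next sentence says that for "changes in ALS disease progression slope as small as 20%, a cohort as large as 700 people with ALS would be required". The paragraph then counts the ALS FRS data as "summarized to 8,400 individual scores over 12 months for 700 patients". It describes the extension's purpose thus: "The goal of the extension study is to enroll a second cohort of participants, a validation cohort".

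Two other places bear on the point. The goals in section A2 speak of recruiting 700 in the second phase "in order to obtain statistically meaningful data for a total of 1000 participants". The phase II consent text in section A3.3.2 says that "participants will be asked to participate in the study for 18 months or until they are no longer able".

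Neither the 450 nor the 700 comes with a significance level, sidedness, power, slope standard deviation, allocation or dropout rate.

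**The concern.** The two sample sizes stand in consecutive sentences and concern the same outcome. The effect falls by a third, from 30% to 20%, but the sample size rises only from 450 to 700, a factor of 1.56. Under the usual inverse-square relation the factor should be 2.25.

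This sentence is the only place in the protocol where an effect size is linked to 700; the data-point counts in the same paragraph merely follow from 700. Section A3.1 gives greater power to detect progression as part of the extension's goal. As written, the protocol therefore credits the extension with a sensitivity that its own benchmark does not support.

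A second difficulty concerns what the figure means. The benchmark comes from clinical trials, where a change in slope is ordinarily a contrast between groups. The extension gives no treatment and compares two measures within the same people. Section A4 mentions selected controls, such as a twin, but describes no comparison of slopes between groups. What a 20% change would be measured against is therefore undefined.

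**Working it through.** **Inputs, all from section A4**
- Benchmark: N = 450, 12 months, 30% change in slope.
- Claim: N = 700, 20% change in slope.
- Basis of the 700: 700 x 12 monthly scores = 8,400, which reproduces the protocol's count. The paragraph therefore uses 12 months for both figures.
- Assumption: significance level, power, relative slope SD, allocation and dropout are the same for both figures. They then cancel in the ratio, and their absence does not affect the result.

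**Attempt to reproduce 700**

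For a difference in mean slopes, N is proportional to (SD/effect)^2.
- N for 20% = 450 x (30/20)^2 = 450 x 2.25 = 1,012.5, so 1,013 (1,014 in two equal arms).
- Shortfall of 700: (1,012.5 - 700)/1,012.5 = 31%.
- Effect detectable with 700 = 30% x sqrt(450/700) = 30% x 0.802 = 24.1%.

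Scaling linearly in the effect gives 450 x 30/20 = 675. That is near 700 but is not a valid rule. On a log-ratio scale, 450 x (ln 0.7/ln 0.8)^2 = 1,150, which is further away.

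**Power for 20% with 700, two-sided 5%**

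Power = Phi[(1.96 + z) x (20/30) x sqrt(700/450) - 1.96], where z belongs to the benchmark's power.
- If the benchmark had 80% power (z = 0.842): Phi(2.802 x 0.8315 - 1.96) = Phi(0.370) = 64%.
- If it had 90% power (z = 1.282): Phi(3.242 x 0.8315 - 1.96) = Phi(0.735) = 77%.

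The protocol does not state the benchmark's power, so these figures hold only under those assumptions.

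**What would have to differ for 700 to be right**
- *Slope variance:* a relative slope SD of sqrt(700/1,012.5) = 0.83 times the benchmark's, i.e. about 17% lower.
- *Dropout:* about 30% built into the 450 and none into the 700, since 1,012.5 x 0.70 = 709.
- *Error rates:* for example, 95% power for the 450 and 85% for the 700, both two-sided 5%, gives 700.
- *Follow-up:* 18 months in place of 12. The sum of squares of time is 182 for months 0 to 12 and 570 for months 0 to 18, a ratio of 0.319. Residual error would have to make up (1 - 700/1,012.5)/(1 - 0.319) = 45% of the 12-month slope variance, with nobody dropping out. If that share is allowed to run from 0% to 100%, N runs from 1,013 down to 323.
- *Pooling both phases:* 1,000 participants correspond to 30% x sqrt(450/1,000) = 20.1%.

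**The case against.** The strongest reply is that the protocol never says 700 was calculated from 450. Both figures may come from the same outside analysis, with different error rates, dropout or populations, and a figure that follows the paragraph is not shown in the text at hand. The extension is also limited to early-stage participants, excluding symptoms beyond 36 months and non-invasive ventilation (section A3.2), so a lower slope variance is conceivable. Participants are asked for 18 months, and the 18-month range for N includes 700. Finally, section A2 speaks of 1,000 participants in total, which on the same scaling comes very close to 20%.

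Part of this stands. A reader might infer that 700 participants are shown to be unable to detect a 20% change. The documents do not support that: they give no variance, power or significance level, and any of the changes listed above could bring 700 and 20% into line.

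The inconsistency itself is not removed. No changed assumption is stated. The paragraph counts 12 months of scores, not 18. It ties 20% to the 700 alone and calls them a second, validation cohort. Pooling would also mix cohorts with different entry criteria.

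A reader might further infer that 20% is the standard the accelerometer must meet. The text says only that a similar design is needed to compare the two measures, and no decision is made to depend on the 20%.

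**Conclusion.** The statement that 700 participants are required for a 20% change in slope is not supported by the benchmark printed beside it. With all other assumptions equal, 20% needs about 1,013, and 700 corresponds to about 24%. This rests on inverse-square scaling and on the same power, significance level, relative slope variance, 12-month follow-up and dropout for both figures. It does not depend on what those values are.

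Even when rescaled, the number describes a between-group trial of the benchmark kind and not the within-person comparison planned here.

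The point is a wording correction to the sample-size rationale. The study gives no treatment, and the rationale sets no test, power or significance level that would have to change.

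**What to change.** In the section A4 rationale, keep 700 and do one of two things.

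1. Restate the detectable change, for example: *Scaling from the benchmark of 450 patients for a 30% change over 12 months, 700 participants correspond to a detectable change in slope of about 24%; 20% would need about 1,013.*
2. If 700 for 20% came from other assumptions, state them (power, significance level, slope variance, follow-up or dropout) and give the resulting calculation.

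In either case add a sentence saying that the figure is a benchmark from between-group clinical trials and not a property of this single untreated cohort. If the pooled 1,000 is mentioned, note that the two phases have different entry criteria. The precision of the paired comparison of ALS FRS with the accelerometer can be left to the statistical analysis plan, because the protocol gives no slope SD or correlation from which to compute it.

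The cost is a change of protocol wording. Under the first option the stated detectable change becomes less favourable, about 24% in place of 20%. No participants are added and no procedures change.
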